## Abstract

**Introduction:**

The main objective of the study will be to evaluate the effects of two widely used standardized mindfulness-based programs [Mindfulness-Based Stress Reduction (MBSR) and Compassion Cultivation Training (CCT)], on epigenetic, neurobiological, psychological, and physiological variables.

**Methods:**

The programs will be offered in an intensive retreat format in a general population sample of healthy volunteer adults. During a 7-day retreat, participants will receive MBSR and CCT in a crossover design where participants complete both programs in random order. After finishing their first 3-day training with one of the two programs, participants will be assigned to the second 3-day training with the second program. The effects of the MBSR and CCT programs, and their combination, will be measured by epigenetic changes (i.e., DNA methylation biomarkers), neurobiological and psychophysiological measures (i.e., EEG resting state, EKG, respiration patterns, and diurnal cortisol slopes), self-report questionnaires belonging to different psychological domains (i.e., mindfulness, compassion, well-being, distress, and general functioning), and stress tasks (i.e., an Arithmetic Stress Test and the retrieval of negative autobiographical memories). These measures will be collected from both groups on the mornings of day 1 (pre-program), day 4 (after finishing the first program and before beginning the second program), and day 7 (post-second program). We will conduct a 3-month and a 12-month follow-up using only the set of self-report measures.

**Discussion:**

This study aims to shed light on the neurobiological and psychological mechanisms linked to meditation and compassion in the general population. The protocol was registered at clinicaltrials.gov (Identifier: NCT05516355; August 23, 2022).

## 1. Introduction

In recent years there has been an outburst of scientific studies on the positive effects of mindfulness-based interventions (Mindfulness-Based Interventions, MBIs) on physical and mental health [1]. Two of the most researched programs related to the development of mindfulness and compassion are, respectively, Mindfulness-Based Stress Reduction (MBSR) [2], focused on attentional training and a non-judgmental attitude, and Compassion Cultivation Training (CTT) [3, 4], more focused on the structured training of a compassionate and self-compassionate attitude. These are highly structured programs, of short duration (i.e., typically delivered in 8 weeks/16 hours format), that have shown positive effects, both for general and clinical populations, as reflected in many meta-analyses and systematic reviews [5–9], including programs using briefer formats (e.g., single-session to 2-week multi-session formats) [10].

The fundamental objective of this study is to explore the potential changes in epigenetic variables, psychological distress, well-being, brain activity, cortisol levels, and reactivity to stress, that can be observed following MBIs. The way to address this question is through an intensive intervention in a retreat format, a procedure that allows control of important variables (e.g., food, environmental conditions, etc.), and administering all the components of the standard MBSR and CCT programs in their entirety. There is already meta-analytic evidence on the positive effects of these intensive multi-day programs in healthy individuals [11]. Although there is some evidence that attentional changes might be involved in the psychological changes observed after a meditation retreat [12], there is a need to examine the mechanisms of action through which meditation practice produces its effects [13]. Most theoretical models published to date emphasize the central role of attention regulation, which is thought to underpin emotional and cognitive flexibility [14], which in turn enhances emotion regulation processes [15], and the ability to maintain non-judgmental awareness of thoughts, feelings, and experiences. Theoretical models also emphasize the role of compassion and self-compassion [16] in promoting change due to MBI practices [17–21]. However, the extant evidence comparing the self-reported psychological effects of MBSR and CCT programs indicates that both programs have similar effects [22, 23], although reached through different mechanisms [24].

Regarding the biological effects of MBIs, there is consistent meta-analytic evidence showing that they produce significant physiological changes in parameters like a reduction in oxygen consumption, blood pressure, and heart rate [25], which are contrary to those that occur during the stress response [26]. These changes have also been observed in three-day intensive meditation retreats [27]. Similarly, although the evidence for brain volumetric change is uncertain [28], there is data on changes in frontoparietal and default network connectivity during resting state tests [29, 30]. There is also promising evidence that intensive intervention practices, in a retreat format, are associated with significant changes in gene expression that might be potentially regulated by epigenetic mechanisms. For example, an 8-day silent guided meditation retreat can modify gene expression, in particular genes related to the immune response [31]. However, the brain mechanisms and molecular activity are not yet well understood. Along the lines of some previous research on detectable epigenetic changes in brief intensive meditation interventions aimed at reducing stress [32–36], we intend to test whether epigenetic changes are one of the mediating mechanisms in the observable psychological changes following an intervention. We will also analyze whether changes in brain connectivity (measured with EEG in resting state) and in the diurnal cortisol rhythms occur throughout the programs.

Although research on the comparative effects of MBSR and CCT has shown the existence of some particular mediators [24], the effects of a sequential intervention of both types of training on the same individuals are not known. This sequential approach is important to evaluate whether there are additive effects of the programs and whether the order of the intervention (one more focused on attentional aspects and the other more on socio-emotional factors) can facilitate psychological and neurobiological changes. Thus, we aim to analyze the existence of differential psychobiological changes in two types of intensive psychological programs (MBSR and CCT), and whether the sequence of the programs (using a cross-over design), does significantly affect the results.

As, to the best of our knowledge, this is the first study using a sequential design with two intensive meditation modalities, it is difficult to formulate specific hypotheses regarding the separate and combined effects of the MBSR and CCT programs on the selected outcomes. Thus, considering the two MBIs jointly, we expect that both programs will significantly: a) modify the DNA methylation and expression levels of specific genes and a reduction of the DNA methylation-based biological clock; b) reduce participants’ levels of psychological distress while increasing their levels of psychological functioning (i.e., mindfulness, compassion, emotion regulation, and well-being); c) change the EEG spectral profile of the resting state brain activity (i.e., changes in the balance between Alpha (8–14 Hz) and Theta (4–8 Hz) frequency bands and, regarding the organization of the brain functional networks, a modulation of the difference between the activation of the default mode network and the one corresponding to the salience network); d) alter awakening and bedtime cortisol levels leading to a steeper Diurnal Cortisol Slope (DCS); e) improve the efficacy of mood regulation following a negative mood induction (using an autobiographical memory task); f) reduce participants’ reactivity in an objective experimental stress test (i.e., Arithmetic Stress Test). In addition, given the multidisciplinary nature of the present project, we intend to provide a comprehensive view of potential changes in various areas of biological and psychological functioning and their interrelationships.

In general, we expect an overall pattern of results in which changes will be significantly higher for the combined effects of both MBIs than for each program separately. Moreover, based on previous literature comparing standard MBSR and CCT programs [24], we expect no major differences in primary outcomes between both programs, although the mechanisms of change may be different; in general, changes in MBSR will be mediated by cognitive variables (e.g., mindfulness) whereas changes in CCT will be mediated by socio-emotional variables (e.g., compassion). We also expect that the self-reported psychological changes associated with the MBIs will remain 3 months after the programs.

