## 2. Methods

### 2.1 Study design overview

We used the SPIRIT reporting guidelines. Participants will be randomly assigned to two groups starting with MBSR or CCT. A stratified randomization procedure, using the Research Randomizer Program (https://www.randomizer.org), performed by the principal investigator (CV), will be used to maintain the same percentage of male and female participants in each group. Participants from both groups will take part in a 7-day retreat, including training in both meditation-based practices. Participants will be blinded to group allocation starting with MBSR or CCT and will not receive any information of any kind about the study hypotheses. (IB and RZ will be in charge of participant recruitment and perform the randomization of each study group). Using a cross-over design, the participants will undergo their second training during the last three days of the retreat. Biological and psychological measures will be collected from both groups in the mornings of day 1 (before beginning the programs), day 4 (after the first program and before the beginning of the second program), and day 7 (at the end of the program). All psychological questionnaires will be administered online. Also, before going to bed, participants will be given a short questionnaire with eight questions about their general functioning during the day and their satisfaction with the progress of the program. Furthermore, a 3-month and a 12-month follow-up assessment will be conducted in both groups only for psychological questionnaires. (See Fig 1).

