#### 2.5.2 Psychological measures

*a) Self-report measures*. Most of these measures were developed in studies with the general population and have been also used in previous MBI studies in healthy individuals [22]. They have shown good or excellent psychometric properties and cover selected psychological distress and functioning constructs (i.e., stress, anxiety, depression, mindfulness, compassion, well-being, and emotion regulation) and all will be administered online via Qualtrics with individualized links (Table 2):

*Psychological distress*. Depression Anxiety Stress Scales (DASS-21) [44, 45].*Psychological well-being*. Satisfaction with Life Scale (SWLS) [46, 47].*Mindfulness*. State Mindfulness Scale (SMS) [48].*Anxiety*. State-Trait Anxiety Inventory (STAI-20) [49, 50].*Somatic Symptoms*. Patient Health Questionnaire (PHQ-15) [51, 52].*Sleep difficulties*. DSM-5 sleep difficulties [53].*Compassion*. State self-compassion State Self-compassion Scale (SSCS) [54, 55].*Fear of Compassion*. The Yourself subscale from the Fear of Compassion Scale [56].*Emotion Regulation*. State Difficulties in Emotion Regulation (S-DERS-21) [57, 58].*Current mood*. Positive and Negative Affect Schedules (PANAS) [59, 60].*Daily assessments of psychological functioning*. A 7-item scale to assess participants’ average state of mindfulness, mind wandering, compassion to others, self-compassion, well-being, the richness of life, and utility of the contents of the program every day.*Affect in the last 3 days*. Hedonic and Arousal Affect Scale (HAAS) [61].*Meditation Adverse Effects*. Meditation-Related Adverse Effects Scale–Mindfulness-Based Program (MRAESMBP) [62].*Program satisfaction*. Client Satisfaction Questionnaire (CSQ-8) [63, 64].

*b) Psychological stress tasks*. ***b*.*1) Stress Reactivity*.** Arithmetic Stress Test: a standardized laboratory stress induction procedure, that is part of the Trier Social Stress Test [65, 66], will be used to assess participants’ stress reactivity. Individuals are asked to repeatedly subtract a given 2-digit number (i.e., 13) from a 4-digit number (e.g., 1022). These numbers were changed for each of the three assessment days. Participants are asked to write their responses on a personal computer as quickly as possible. Time is limited to 3 minutes to increase the stressful nature of the task. Pre-post stress level changes in mood will be assessed with the PANAS and STAI.

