### 2.7 Statistical analysis plan

Independent t-tests for continuous data and chi-square test (χ2) for categorical data will be conducted to confirm that there were no demographic or clinical differences between groups at baseline. Repeated-measures ANOVAs will be conducted to analyse changes associated with the programs. For the autobiographical memory task and all the biological measures (i.e., genetic measures, EEG, EKG, respiratory rate, and cortisol in saliva), a 2 (Order of program) x 3 (Time) repeated measures ANOVA will be conducted. For the self-report psychological measures, a 2 (Order of program) x 4 (Time) ANOVA will be conducted. We will use age, sex, and previous meditation experience as covariates in the main analyses. Assumptions of normality, homogeneity of variances, sphericity, and homogeneity of covariances will be checked. Further analyses will include post-hoc, p-corrected comparisons (e.g., Bonferroni). All analyses will be performed with SPSS 28.0 (IBM Corp., 2021) or R Studio statistical software (R Core Team, 2021). Two-tailed tests will be used to determine significance at the 5% level.

The EPIC methylation arrays´ raw data will be normalised and filtered by a robust bioinformatics pipeline procedure [69]. We will then perform an unsupervised analysis of the data via hierarchical clustering, i.e., PCA and t-SNE (by R Studio). In parallel, taking advantage of the known DNA methylation signatures related to distinct cell types or molecular processes, we will: 1) characterize the proportion of different immune cells, and 2) determine the epigenetic age with Horvath’s model or other epigenetic clocks to capture the influence of lifestyle on the DNA methylome [70, 71]. This may reveal a link between the MBI programs and the immune response, inflammation, and cells’ physiological condition. Finally, we will focus on supervised analyses to identify differential DNA methylation biomarkers in the two groups (MBRS first *vs* CCT first) and time points: day 1(baseline), day 4 (program switch), and day 7 (post retreat).

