To summarize, this is an innovative study aimed at testing the effect of two standard meditation interventions (MBSR and CCT), administered in an intensive retreat format. There is an increasing need for interventions to improve the well-being of the population in a variety of formats. The administration of meditation programs in a relatively short retreat may be an important contribution to meditation studies in the general healthy population. In addition, the cross-over design of the study will provide insight into whether the order of the interventions (MBSR first or CCT first) may play a role in the delivery of these interventions. The design may also help to answer some basic questions in meditation research regarding the ingredients and sequence of the components of these interventions. Thus, our study could pave the way for more nuanced research into meditation-based interventions, especially in terms of optimizing intervention sequences for maximal benefit.

Given the increasing popularity of mindfulness and compassion practices and research in the general population, it is crucial to understand their effects on individuals who do not necessarily have clinical problems but seek personal growth, stress reduction, or well-being enhancement [5, 81–83]. We hope that the rigorous approach of this study ensures the integrity of our findings, free from potential confounders related to health conditions. By understanding the effects of two consecutive interventions on a healthy cohort, we might offer evidence-based guidance on how these practices can serve as preventative measures for the broader community, potentially enhancing its well-being, and perhaps reducing the onset of mental health conditions, We also hope that, despite the potential limitations acknowledged in our design, the results generated by this ambitious study may shed light on the neurobiological and psychological mechanisms linked to meditation and compassion in the general population and may contribute to improving the scientific basis of these practices.

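### For outcomes measured only in the retreat, program order cannot be told apart from the most recent program, and the planned Order x Time tests also pick up the Day-4 program difference

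*Protocol article*

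**What the plan says.** **Aim.** Section 1 asks "whether the sequence of the programs (using a cross-over design), does significantly affect the results", and whether order "can facilitate psychological and neurobiological changes", so biological outcomes are within the question. Section 3 names order as the second of two main aspects and hopes the study will help with "optimizing intervention sequences for maximal benefit".

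**Timing.** Section 2.1 places the later in-retreat measurements at "day 4 (after the first program and before the beginning of the second program), and day 7 (at the end of the program". Section 2.2 gives a half-day break between programs and no longer wash-out.

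**Follow-up.** According to section 2.1, "a 3-month and a 12-month follow-up assessment will be conducted in both groups only for psychological questionnaires". Table 2 shows no epigenetic, EEG, EKG, respiration, cortisol or task measurement after Day 7, and section 3 lists this as a limitation.

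**Analysis.** For the autobiographical memory task and the biological measures, section 2.7 states that "a 2 (Order of program) x 3 (Time) repeated measures ANOVA will be conducted". Self-report measures get a 2 (Order) x 4 (Time) ANOVA; the four times are not listed. The section does not say which term or contrast answers the order question, and it does not separate order from the program just completed.

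**Expected program differences.** Section 1 expects none of importance in the primary outcomes, but expects that "changes in MBSR will be mediated by cognitive variables (e.g., mindfulness) whereas changes in CCT will be mediated by socio-emotional variables (e.g., compassion").

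**The concern.** A sequence exists only once both programs have been taken. At Day 4 each participant has had one program, so the difference between order groups is MBSR against CCT. At Day 7 both sequences are complete, but the MBSR-first group has just left CCT and the CCT-first group has just left MBSR. Unless the first program's effect is fully kept, or the programs have equal effects, that difference mixes order with recency.

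An Order x Time interaction over Days 1, 4 and 7 takes in both contrasts. It can be significant because the programs differ, because recent training weighs more, or because sequence matters, and nothing in the test tells these apart. Since the study hopes to inform the choice of sequence, a program or recency difference could be taken as advice on order, and its sign could favor whichever program came last.

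**Working it through.** **Inputs from the article.** 26 per group, two-sided 5% (sections 2.3 and 2.7); assessments on Days 1, 4 and 7 for in-retreat outcomes, plus 3 and 12 months for questionnaires (section 2.1, Table 2). The plan gives no figure for an order contrast to reproduce. Of the sample size, only the final step can be checked: 21 x 1.2 = 25.2, rounded up to 26. The 21 itself cannot be confirmed or faulted, because the effect-size metric, the tested effect and the correlation are not given.

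**Assumptions.** SD 1; correlation ρ of 0.5 or 0.7 between any two times; program difference d of 0.2 or 0.37 SD; retention λ (the share of the first program's effect still present at Day 7) of 0, 0.5 or 1, equal for both programs; no true sequence effect. The 0.37 is borrowed from section 2.3, where it is a retreat effect on well-being, not an MBSR–CCT difference. The four times are taken as Days 1, 4, 7 and 3 months, with no group difference at 3 months. The planned covariates are not modelled.

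**Algebra.** Let m and c be the effects of MBSR and CCT, d = m − c, and s the sequence effect. All contrasts are MBSR-first minus CCT-first.

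- Day 4: D4 = m − c = d.
- Day 7: D7 = (λm + c + s) − (λc + m) = s − (1 − λ)d.
- Sum: D4 + D7 = s + λd.

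With s = 0 and d = 0.37, D7 is −0.37 (λ = 0), −0.185 (λ = 0.5) or 0 (λ = 1).

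**Size of the Day-7 test.** The standard error of the baseline-adjusted contrast is about √(2(1 − ρ²)/26):

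- ρ = 0.5: √(1.5/26) = 0.240, so 0.37/0.240 = 1.54 standard errors.
- ρ = 0.7: √(1.02/26) = 0.198, so 0.37/0.198 = 1.87 standard errors.

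**Simulated rejection rates with no sequence effect** (20,000 trials per cell; ρ = 0.5 / 0.7; separate runs differ by a point or two):

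| d | λ | 2 x 3 Order x Time | 2 x 4 Order x Time | Adjusted Day 7 | Adjusted 3 months |
|---|---|---|---|---|---|
| 0.37 | 0 | 65% / 87% | 58% / 82% | 32% / 45% | 5% / 5% |
| 0.37 | 0.5 | 42% / 63% | 37% / 58% | 12% / 15% | 5% / 5% |
| 0.37 | 1 | 26% / 40% | 24% / 39% | 5% / 5% | 5% / 5% |
| 0.2 | 0 | 23% / 35% | 19% / 31% | 13% / 17% | 5% / 5% |

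With d = 0 every test holds about 5%. At λ = 1 the Day-7 contrast is clean but Order x Time is not, because D4 is still in it. Adding a 3-month column to the omnibus test does not remove the problem.

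**Is the 3-month contrast free of recency?** Let x be the share of an effect kept over three days under exponential decay. Ninety days is 30 such steps, so the leftover recency contrast is d(1 − x)x³⁰. This is largest at x = 30/31: (1/31)(30/31)³⁰ = 0.012. At most 1.2% of d remains, or 0.0045 SD for d = 0.37.

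**Power of the 3-month contrast.** A true 3-month order difference of 0.37 SD has the same standard error as above, so power is about 32% (ρ = 0.5) to 45% (ρ = 0.7) at 26 per group. Without baseline adjustment it is 26%.

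**The case against.** **Order is randomized.** The Day-7 difference is therefore an unbiased estimate of the effect of the assigned sequence on the state at the end of the retreat, and that is one fair reading of the aim. This stands. What it does not support is reading the difference as a sequence effect apart from recency, which is what the wish to understand and optimize sequencing needs.

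**The programs may hardly differ.** The article expects no major difference in primary outcomes, and at d = 0.2 the Day-7 rate is only 13–17% even with no retention. This limits the size. It does not cover the mindfulness and compassion scales, for which section 1 implies different effects, and the study also aims to find differential program changes.

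**A condensed article may leave contrasts to a fuller plan.** True, and the lack of a named contrast is not the complaint. The point concerns the Order x Time tests that section 2.7 does fix.

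Four stronger readings are tempting but not supported:

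- *Order can be read only at Day 7.* This holds for biological measures and tasks. Self-report scales with follow-up are also planned at 3 and 12 months in both order groups.
- *The plan reports the Day-7 difference as an order effect.* Nowhere does the article make Day 7, or any one contrast, the answer to the order question.
- *The Hedonic and Arousal Affect Scale, described as "Affect in the last 3 days", carries nothing from the first program at Day 7.* That is a recall window. A lasting change from the first program could still shape affect in those days.
- *The sequence effect always lies between D7 and D4 + D7.* This needs equal retention for both programs. With equal program effects e but retentions λM and λC, D4 = 0 and both figures equal s + (λM − λC)e. For e = 0.5 and retention 0.8 against 0.2, the shift is 0.30 SD. A rule requiring both figures to exclude zero in the same direction then gives 9–12% false claims, and 23–30% at 1 against 0. With equal programs and s = 0.5 SD, it also cuts power from 53–70% to 22–31%.

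**Conclusion.** The point holds in a limited form. For biological measures and laboratory tasks, order and most recent program are fully aliased at Day 7, and no later measurement can separate them. The planned Order x Time tests are affected more, for self-report scales measured on Day 4 as well, because they also take in the Day-4 program difference.

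The harm depends on a real program difference. Order x Time is then affected at any retention; the Day-7 contrast is affected only if the first program's effect partly fades. The article gives neither quantity, so the rates above show what could happen under stated assumptions and are not a forecast. The self-report part of the aim can be rescued with data already planned. The neurobiological part can only be labelled honestly. This is an inexpensive correction to section 2.7 and does not invalidate the design.

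**What to change.** In section 2.7:

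1. For self-report scales with follow-up, prespecify the baseline-adjusted MBSR-first minus CCT-first difference at 3 months as the test of lasting order, with 12 months as support. State that power is only about 32–45% for a 0.37 SD difference, so a null result would not show that order is irrelevant.
2. For in-retreat outcomes, do not take the omnibus Order x Time test as evidence of order. Report the Day-7 difference with its confidence interval and label it *order or most recent program*.
3. Optionally add D4 + D7 as a sensitivity figure where a Day-4 value exists (the PHQ-9, PHQ-15 and SWLS have none). State that it acts as a bound only if both programs' effects are retained equally, and do not build a decision rule on it.

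The affect scale covering the last three days can stay in the analysis under the same label. No new visits or measurements are needed. The cost is wording and more cautious order claims for in-retreat outcomes.
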